### Description of the Intervention

Participants wore orthokeratology lenses for 8 to 10 hours per night for at least 1 month.

#### Lens Fitting Criteria

Paragon CRT orthokeratology lenses were fitted by the principal investigator following standard orthokeratology fitting procedures. Lens fit was assessed by evaluating the fluorescein pattern under slit-lamp examination to confirm adequate central support, midperipheral alignment, and peripheral clearance. Treatment centration was assessed at each follow-up visit using 2 complementary methods: slit-lamp evaluation of the fluorescein pattern and topographic analysis of the treatment zone using axial and tangential maps obtained with the Pentacam system, which allowed objective verification of the treatment zone centration relative to the corneal apex. Participants exhibiting radial decentration greater than 0.5 mm were excluded from the study.

#### Adherence Monitoring

Compliance with overnight contact lens use was monitored at each follow-up visit using a structured questionnaire, a daily wear diary completed by the participant and their parent or legal guardian, and direct questions asked of the parents at each visit. A minimum wearing time of 8 hours per night was considered necessary; participants who consistently wore contact lenses for less than 8 hours were considered noncompliant and were excluded from the analysis.

#### Discontinuation Criteria

Participants were excluded from the study if any of the following situations occurred: lens decentration greater than 0.5 mm radially, eye infection, lens intolerance, any adverse ocular event, or voluntary withdrawal from the study at any time.

#### Adverse Event Monitoring

Any adverse events occurring during the study period were recorded in the participant’s clinical record and reported to the Drug Research Ethics Committee (*Comité de Ética de la Investigación con medicamentos* [CEIm]) of the Pere Virgili Institute for Health Research (*Institut d'Investigació Sanitària Pere Virgili* [IISPV]) in accordance with applicable regulations. The principal investigator was responsible for identifying, evaluating, and reporting all adverse events.

### Study Variables and Data Sources

#### Personal Variables

These include age (measured in years) and sex (female or male).

#### Ocular Variables

Ocular variables comprise epithelial thickness, corneal power, corneal asphericity, myopia and astigmatism, pupil diameter, topographic changes, and corneal aberrations, defined as follows:

Epithelial thickness is measured in microns, along with total corneal thickness (pachymetry).Corneal power is expressed as TCRP, obtained from the Pentacam tomographic system. TCRP incorporates both the anterior and posterior corneal surfaces together with corneal pachymetry, using the true corneal refractive index of 1.376, thereby providing a more accurate representation of corneal optical power than conventional keratometric indices. TCRP values are extracted for corneal diameters of 3, 5, and 7 mm. Simulated keratometry (Sim-K) values are not used.Corneal asphericity is expressed as the Q value, obtained from the Pentacam tomographic system for the anterior corneal surface. A negative Q value denotes a prolate cornea, steeper centrally and flatter peripherally, whereas a positive Q value denotes an oblate cornea.Myopia and astigmatism are measured in diopters.Pupil diameter is measured under photopic, mesopic, and scotopic conditions (in mm) using the MYAH myopia management system, which incorporates an integrated pupillometer that allows dynamic pupil diameter assessment under standardized luminance conditions.Topographic changes, comprising corneal aberrations and corneal refractive power, are measured in the morning, 1 to 3 hours after lens removal, at all time points.Higher-order corneal aberrations are analyzed using Zernike coefficients obtained from the Pentacam for pupil diameters of 3, 5, and 7 mm.

The specific aberrations analyzed are the fourth-order spherical aberration z(4,0), expressed in microns; the spherical-like aberration of orders 4 and 6, represented by its RMS and calculated as the square root of the sum of the squares of z(4,0) and z(6,0), expressed in microns; the third-order coma aberration, represented by its RMS and expressed in microns as the square root of the sum of the squares of z(3,−1) and z(1,3); the coma-like aberration of orders 3 and 5, represented by its RMS expressed in microns as the square root of the sum of the squares of z(3,−1), z(1,3), z(5,−1), and z(1,5); the third-order RMS aberration, expressed in microns as the square root of the sum of the squares of z(3,−3), z(3,−1), z(1,3), and z(3,3); the fourth-order RMS aberration, represented in microns as the square root of the sum of the squares of z(4,−4), z(4,−2), z(4,0), z(2,4), and z(4,4); and the total HOA RMS from the third to the sixth order, represented in microns as the square root of the sum of the squares of all Zernike coefficients from orders 3, 4, 5, and 6.

### Statistical Analysis

Quantitative data following a normal distribution will be presented as means (SDs), while nonnormally distributed quantitative data will be expressed as medians (IQRs). The normality of the variables will be assessed using the Kolmogorov-Smirnov test. Categorical data will be reported as frequencies and percentages.

The unit of analysis will be the eye, including both eyes of each participant. To account for the nonindependence of contralateral eyes in the same participant’s within-subject repeated measurements, the primary and secondary outcomes will be analyzed using linear mixed-effects models with a fixed effect for time (baseline vs 1 month) and a random intercept for each participant. Results will be presented as estimated mean differences with 95% CIs. Model assumptions (normality and homoscedasticity of the residuals) will be assessed graphically, and in the event of substantial noncompliance, a generalized estimating equations (GEE) approach with an interchangeable working correlation structure and robust SEs will be used as a sensitivity analysis. Missing data will be treated under the missing at random (MAR) assumption inherent in mixed models, without imputation; the number of eyes and participants providing data at each time point will be reported. Given the presence of multiple secondary outcomes, we will apply the Benjamini-Hochberg false discovery rate procedure to control for multiplicity. A significance level of *P*<.05 will be applied in all cases.

Given the sample size of 23 participants, multivariable regression analysis will not be performed, as the number of observations would be insufficient to support stable and reliable regression models without introducing the risk of overfitting.

The follow-up visits, performed 1 night and 1 week after lens fitting, were conducted solely for the purpose of evaluating clinical safety and adaptation. Measurements of the primary and secondary outcomes were obtained at baseline and at 1 month, constituting a single pre-post comparative period that will be evaluated using the aforementioned mixed-effects models. This manuscript was prepared in accordance with the TREND (Transparent Reporting of Evaluations with Nonrandomized Designs) guidelines for quasi-experimental studies.

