## Methods

### Study Objectives

The primary objective of this study is to determine the change in anterior corneal spherical aberration, defined as the Zernike coefficient z(4,0) measured at a 7-mm pupil diameter, after 1 month of overnight orthokeratology.

The secondary objectives are to analyze changes in refractive maps obtained using the Pentacam topographic system (OCULUS Optikgeräte GmbH), including TCRP and corneal asphericity; to assess corneal aberrations through Zernike analysis at the remaining pupil diameters, examining the relationship between changes in anterior corneal asphericity and induced spherical aberration; and to evaluate changes in central and peripheral epithelial thickness using corneal optical coherence tomography (OCT) and their correlation with changes in corneal asphericity and induced aberrations.

For clarity, the primary outcome of the study is the change in anterior corneal spherical aberration z(4,0) at a 7-mm pupil diameter, from baseline to the 1-month follow-up visit. All remaining measures constitute secondary outcomes, namely, anterior corneal spherical aberration z(4,0) at 3-mm and 5-mm pupil diameters; spherical-like, coma, coma-like, third-order root mean square (RMS), fourth-order RMS, and total HOA RMS at all 3 pupil diameters; TCRP at 3, 5, and 7 mm; corneal asphericity (Q value); and central and peripheral epithelial thickness. Axial length is reported for descriptive purposes only and does not constitute an outcome measure.

Cycloplegic refraction was performed at the baseline visit only, to confirm the degree of myopia for eligibility assessment and, together with corneal topography, to inform the orthokeratology lens design. It was not repeated at follow-up visits and was not used as a correlational variable in the analysis of posttreatment corneal changes.

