### Sample Size

The sample size was determined based on changes in anterior corneal spherical aberration (Zernike coefficient z[4,0], expressed in microns), as it is one of the HOAs most strongly associated with optical quality after orthokeratology. The threshold of 0.14 μm was derived from the Rayleigh criterion (λ/4) and was used as an optical reference value for sample size estimation, rather than as a validated clinical threshold for visual quality. This criterion establishes that an increase in spherical aberration exceeding one quarter of the wavelength of light deteriorates optical quality.

Using a reference wavelength (λ) of 0.555 μm (peak sensitivity of the human visual system), this yields a threshold of 0.555/4≈0.14 μm.

With a 2-sided α of 0.05 (type I error) and a β of 0.05 (type II error), corresponding to a statistical power of 95%, and an assumed SD of 0.166 μm, a minimum of 19 participants was required. Considering a 20% loss to follow-up rate, a total of 23 participants were recruited.

The sample size was calculated using GRANMO (version 8; Municipal Institute of Medical Research) [14].

This calculation was based exclusively on the primary outcome (anterior corneal spherical aberration).

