The quasi-experimental pre-post design lacks a concurrent control group. Consequently, observed changes cannot be attributed exclusively to the intervention, as confounding factors such as physiological corneal variation over time or regression to the mean cannot be fully excluded. The relatively short follow-up period of 1 month, while sufficient to capture early optical changes, does not allow the assessment of long-term stability or reversibility of the observed effects. Additionally, the study cohort presents inherent heterogeneity due to the wide age range of participants (aged 8-21 years). Although we acknowledge that corneal biomechanics and epithelial remodeling rates may differ across developmental stages, all participants will be analyzed as a single cohort without age-based stratification. We maintain this approach because the primary outcome—anterior corneal spherical aberration—is predominantly determined by the magnitude of myopic correction and lens design parameters rather than age. To our knowledge, no previous study has specifically demonstrated age-dependent variation in epithelial remodeling or aberrometric response within this age range. Although age is reported as a descriptive variable, future research with larger sample sizes should incorporate age-stratified analyses to formally explore potential variations in epithelial remodeling dynamics across developmental stages.

Accordingly, the findings should be interpreted as a pooled population-level effect across a heterogeneous age range rather than as an age-specific estimate. An adequately powered age-stratified analysis would require approximately 25 to 30 participants per subgroup, corresponding to a total sample of 50 to 60 participants, and remains a clear priority for future studies.

Cycloplegic refraction was performed at the baseline visit only to confirm eligibility and to inform orthokeratology lens design and was not repeated at follow-up. Consequently, changes in the components of refractive error cannot be assessed. Refraction measured over a cornea recently reshaped by orthokeratology is of limited reliability, and repeated cycloplegia in a pediatric population entails additional burden; nevertheless, future studies incorporating repeated refraction, where clinically appropriate, would allow this question to be addressed.

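### The participant random intercept drops out of the baseline-to-1-month contrast, so the primary model does not account for correlated change in a participant's two eyes

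*Protocol article*

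**What the plan says.** The Protocol article's Study Objectives section states that "the primary outcome of the study is the change in anterior corneal spherical aberration z(4,0) at a 7-mm pupil diameter"; the change is taken over the first month of wear. Under Statistical Analysis, "The unit of analysis will be the eye, including both eyes of each participant", and the data for the model come from two visits: "Measurements of the primary and secondary outcomes were obtained at baseline and at 1 month, constituting a single pre-post comparative period". Each participant with complete data therefore contributes four values.

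The model for the primary and all secondary outcomes, given in the same words in the Abstract, is "linear mixed-effects models with a fixed effect for time (baseline vs 1 month) and a random intercept for each participant". The stated purpose is to handle the dependence between fellow eyes and between repeated measurements. No other random effect is named, and no robust variance is specified for the primary analysis.

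The only safeguard is a check of the residuals: "Model assumptions (normality and homoscedasticity of the residuals) will be assessed graphically". After that, "in the event of substantial noncompliance, a generalized estimating equations (GEE) approach with an interchangeable working correlation structure and robust SEs will be used"; the GEE is given the status of a sensitivity analysis only.

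**The concern.** A random intercept per participant describes how a person's general level differs from the average. The estimand is a change within the person, and the general level subtracts out of it. Two other things determine the precision of the estimated change:

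- whether a participant's two eyes change by similar amounts, which is a participant-by-time effect;
- whether stable right-left differences are kept out of the residual, which needs an eye-within-participant effect.

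The model has neither term. Omitting the first makes the SE too small; omitting the second makes it too large.

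Correlated change is the natural expectation here. The Introduction links the induced aberration to the degree of myopic correction, and Strengths and Limitations says that the primary outcome "is predominantly determined by the magnitude of myopic correction and lens design parameters rather than age". Fellow eyes usually need similar correction. They also normally share the night's wearing time and the delay between lens removal and measurement.

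At stake are the 95% CI and P value of the primary result. The same model produces every secondary P value entering the Benjamini-Hochberg step, and that step cannot repair invalid inputs. The planned residual plots look at normality and constant variance, so they would not show the problem or trigger the robust analysis.

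**Working it through.** **Inputs from the Protocol article (Sample Size, Statistical Analysis):** effect 0.14 μm, SD 0.166 μm, two-sided α 0.05, power 95%, 19 participants required, 23 recruited; two eyes and two visits per participant.

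**Assumptions not in the documents:** inter-eye correlation of change ρ from 0 to 0.9; baseline SD 0.05 to 0.20 μm; baseline inter-eye correlation 0.5 to 0.9; change independent of baseline; complete data.

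**Reproducing the plan's figure.** The paired formula gives n = [(1.960 + 1.645) × 0.166 / 0.14]² = 18.27, rounded up to 19; 19 × 1.2 = 22.8, hence 23. This agrees with reading 0.166 as the SD of the change (SDd). I apply it per eye.

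**Algebra.** After the participant mean is removed, three orthonormal contrasts remain per participant:

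- T, the mean change of the two eyes: var(T) = SDd²(1+ρ)/2
- H, half the difference between the two eyes' changes: var(H) = SDd²(1−ρ)/2
- M, the time-averaged right-left difference: var(M) = 2 × (baseline SD)² × (1 − baseline inter-eye correlation) + var(H)

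The participant intercept appears in none of them. The estimate is the average of T, so its true variance is var(T)/n. The stated model assumes that T, H and M share one residual variance and pools them:

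s² = [(n−1)var(T) + n·var(H) + n·var(M)] / (3n−1), with reported variance s²/n on 3n−1 degrees of freedom.

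For large n, reported variance / true variance = [var(T) + var(H) + var(M)] / [3 var(T)].

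**Numbers at n = 23, baseline SD 0.10, baseline inter-eye correlation 0.8** (SDd² = 0.027556):

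| | ρ = 0.5 | ρ = 0.8 |
|---|---|---|
| var(T) | 0.02067 | 0.02480 |
| var(H) | 0.00689 | 0.00276 |
| var(M) = 0.00400 + var(H) | 0.01089 | 0.00676 |
| True SE = √(var(T)/23) | 0.0300 | 0.0328 |
| Model SE = √(s²/23), divisor 3n−1 = 68 | 0.0235 | 0.0221 |
| Ratio | 0.78 | 0.67 |
| Simulated coverage of the 95% CI | about 88% | about 81% |
| CI half-width, model (t on 68 df) | 0.047 | 0.044 |
| CI half-width, participant means (t on 22 df) | 0.062 | 0.068 |

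Type I error is thus about 12% and 19% instead of 5%. Fitting the stated model in standard mixed-model software at ρ = 0.8 (200 simulated trials) gave a mean SE of 0.022 against an empirical SD of 0.034, with coverage 83.5%.

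**No stable right-left difference (n = 23):**

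| ρ | Model SE | True SE | Type I error |
|---|---|---|---|
| 0 | 0.0245 | 0.0245 | 4.9% |
| 0.3 | 0.0231 | 0.0279 | 10.7% |
| 0.5 | 0.0222 | 0.0300 | 14.5% |
| 0.7 | 0.0212 | 0.0319 | 19.3% |
| 0.9 | 0.0202 | 0.0337 | 24.4% |

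**Opposite direction.** With baseline SD 0.20, baseline inter-eye correlation 0.5 and ρ = 0, the ratio is about 1.40 and coverage 99%.

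**Whole range.** Over the assumed ranges the ratio runs from about 0.60 to about 1.40 and coverage from 76% to 99%. A t interval on participant-mean change held about 95% throughout.

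**Does the larger model repair it?** In two example data sets (ρ = 0.7), a mixed model with eye and participant-by-time terms gave SEs of 0.0234 and 0.0362. The participant-mean analysis gave 0.0235 and 0.0362; the stated model gave 0.0171 and 0.0322.

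**The case against.** The other side has fair points.

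- **Direction and size are not fixed by the documents.** The two omissions can cancel. With baseline SD 0.20 and baseline inter-eye correlation 0.5, the ratio is 0.97 at ρ = 0.8 and 1.10 at ρ = 0.5. This stands, and it is why a range is given. A model whose CI is right only by coincidence is still misspecified.
- **Not every shared feature creates correlation.** One lens brand for everyone shifts the mean change without tying fellow eyes together, the protocol itself discounts age, and wearing time was restricted to 8 to 10 hours. That stands too. Similar myopic correction in fellow eyes is the best-supported reason, with shared wear and measurement timing behind it.
- **The main conclusion would probably survive.** Even at ρ = 1 the true SE is 0.166/√23 = 0.0346, so 0.14 μm lies 4.0 SEs from zero and power is 97%. At 19 completers and ρ = 0.8 it lies 3.9 SEs away, with 96% power. The point estimate is also unaffected for balanced data. But the protocol promises mean differences with 95% CIs, and weaker secondary effects have no such margin.
- **GEE with robust SEs is already named.** Clustered on participant, it would address the problem. As written it is only a sensitivity analysis, with a trigger that does not respond to a wrong correlation structure.
- **Cancellation is exact only with complete data.** With some 1-month values missing, the intercept contributes a little information. The two missing variance terms remain missing.

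**Conclusion.** The concern holds. The model is stated in full and does not do what the article says it does: for complete data it forces zero correlation between the two eyes' changes and counts stable right-left differences as noise.

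At moderate to high inter-eye correlation of change (0.5 to 0.8), with modest stable right-left differences, the primary CI would be about a quarter to a third too narrow (0.047 against 0.062, and 0.044 against 0.068). Nominal 95% coverage would be about 88% to 81%. If stable right-left differences dominate, the interval is too wide instead.

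These sizes rest on reading 0.166 μm as the eye-level SD of change and on variance components that the documents do not give. That the intercept cancels rests on none of these. Because the validity of the primary interval and of all secondary P values is affected, this must be corrected before results are reported.

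**What to change.** Replace the model for the primary and secondary outcomes with one that has a participant random intercept, a participant random slope for time and an eye-within-participant random intercept, using Kenward-Roger degrees of freedom. This keeps participants with incomplete data, as the plan's missing-at-random approach intends.

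Name as the fallback, if that model fails to converge or a variance estimate falls on the boundary, the average of the two eyes within participant at each visit, with the participant-level change analysed by a t interval on n−1 degrees of freedom. With 19 to 23 participants this simpler analysis would also be a sound primary choice; for complete pairs the two agree when the variance estimates are not on the boundary.

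If GEE is kept, cluster on participant, apply a small-sample correction and report it regardless of the residual plots.

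Correct the sentence that credits the random intercept with handling fellow-eye dependence, in both the Abstract and Statistical Analysis. The Results section says analysis is under way, so date the change and make it before the primary estimate is read.

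The cost is a sentence or two and a few lines of code, with no new data. The price is an honest, usually wider, interval.

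### The fallback GEE names robust standard errors without a small-sample correction for about 18 to 23 participants; in its usual form its 5% tests run at about 7%

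*Protocol article*

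**What the plan says.** The Statistical Analysis section makes linear mixed-effects models the analysis of the primary and secondary outcomes. Normality and homoscedasticity of the residuals are to be judged graphically. If they fail substantially, a GEE with "an interchangeable working correlation structure and robust SEs will be used as a sensitivity analysis". The section does not say whether these standard errors are corrected for a small number of clusters, or whether tests and intervals use a normal or a t reference.

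On the amount of data, the same section states: "The unit of analysis will be the eye, including both eyes of each participant". The Sample Size section gives "an assumed SD of 0.166 μm, a minimum of 19 participants was required" and continues: "Considering a 20% loss to follow-up rate, a total of 23 participants were recruited". The authors do treat the sample as small elsewhere: the paragraph that rules out multivariable regression opens with "Given the sample size of 23 participants".

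**The concern.** The sandwich variance is justified as the number of independent clusters grows. Here the cluster is the participant. A second eye and a second visit add observations within a cluster but no clusters. With about 20 clusters the uncorrected sandwich is biased downward, and a normal reference ignores the uncertainty in the variance estimate. Both errors make intervals too narrow and P values too small.

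The GEE is the only alternative model that the article names for use when the mixed model fails its checks. A sensitivity analysis that leans towards significance can seem to confirm a change that a calibrated analysis would leave uncertain.

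**Working it through.** **Inputs.** From Sample Size: two-sided α 0.05, power 95%, change 0.14 μm, SD 0.166 μm (taken here as the SD of the change), 19 evaluable, 23 recruited, 20% loss. From Statistical Analysis: two eyes and two visits, so up to four observations per participant.

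**The plan's own figure.** n = ((1.960 + 1.645) × 0.166/0.14)² = 18.27, rounded up to 19, as stated. Then 18.27/0.8 = 22.8, giving 23. The calculation is therefore that of a one-sample (paired) change with the participant as the unit. With 20% loss, 23 × 0.8 = 18.4, so about 18 to 23 clusters reach the analysis.

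**Reduction of the GEE.** With complete data the GEE time effect is the mean of the participants' two-eye mean changes. Write s for the SD of those changes (divisor n−1). Then:

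- uncorrected robust SE = √((n−1)/n) × s/√n, used with 1.960;
- exact interval under normality: s/√n, used with t(0.975, n−1);
- width ratio = 1.960 × √((n−1)/n) / t(0.975, n−1);
- actual size = 2 × P(t(n−1) > 1.960 × √((n−1)/n)).

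| n | 1.960 × √((n−1)/n) | t(0.975, n−1) | Width ratio | Too narrow by | Actual size |
|---|---|---|---|---|---|
| 18 | 1.905 | 2.110 | 0.903 | 9.7% | 7.4% |
| 19 | 1.908 | 2.101 | 0.908 | 9.2% | 7.3% |
| 23 | 1.917 | 2.074 | 0.924 | 7.6% | 6.8% |

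**Check by fitting the GEE.** Exchangeable GEEs fitted to simulated two-eye, two-visit normal data (1,200 replicates) rejected in 7.8% (n=23) and 8.9% (n=18), with a Monte Carlo error of about 0.8 points. With 18 complete participants plus 5 seen only at baseline the figure was 6.4%. These agree with the closed form within about two Monte Carlo standard errors.

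**Non-normal changes (assumed; the documents give no shape).** Simulation with 200,000 replicates per cell:

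| Participant-level change | Uncorrected, normal reference: n=23 / n=18 | Divisor n−1, t reference: n=23 / n=18 |
|---|---|---|
| Skewness 1 | 7.5% / 8.2% | 5.7% / 5.9% |
| Skewness 2 | 9.7% / 10.6% | 7.9% / 8.3% |
| Symmetric, heavy tails (t, 3 df) | 6.2% / 6.6% | 4.4% / 4.2% |

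At skewness 2 and n=18, the choice of standard error and reference accounts for 10.6 − 8.3 = 2.3 points of the 5.6-point excess. The other 3.3 points come from the skewness. With heavy symmetric tails the inflation is smaller than under normality.

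**Size on the outcome scale.** At n=19 with SD 0.166 μm, s/√n = 0.0381 μm. The half-width is 1.908 × 0.0381 = 0.073 μm uncorrected and 2.101 × 0.0381 = 0.080 μm exact.

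**The case against.** The strongest reply is that the article never says the standard errors are uncorrected. Corrected sandwich estimators are also robust standard errors, and an analysis plan that is not shown could name one. This stands as a limit: the miscalibration is conditional on the usual reading of an unqualified term. It does not remove the point, because the article does specify the estimator, the working correlation and the type of standard error. An analyst who follows those words with common defaults gets the intervals described.

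The practical effect on the primary outcome is also small. The half-widths differ by 0.007 μm against a reference change of 0.14 μm. At that change and n=19 the t statistic is 0.14/0.0381 = 3.7, so the conclusion would not turn on the choice. This stands too. The effect would matter only for borderline results.

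Three stronger readings are tempting, and the document does not support them:

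- *A reader might infer that the main result is compromised.* The mixed model remains the stated analysis, and the GEE is a conditional sensitivity analysis beside it.
- *A reader might infer that GEE P values feed the Benjamini-Hochberg procedure and loosen it.* The article applies that procedure to the secondary outcomes, whose stated analysis is the mixed model. It nowhere says that GEE P values enter.
- *A reader might infer that the GEE runs only on non-normal data, where it does worst.* Unequal residual variance alone can trigger it. Non-normal residuals need not mean skewed participant-level changes, and symmetric heavy tails reduce the inflation.

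**Conclusion.** The point holds and is minor. Run with an uncorrected sandwich and a normal reference on 18 to 23 participants, the fallback GEE gives 95% intervals 7.6% to 9.7% too narrow and a type I error of 6.8% to 7.4%. This assumes complete two-eye, two-visit data and normal participant-level changes. An error rate of 8% to 11% should be quoted only with its assumption of skewness 1 to 2, and with the note that a t reference with divisor n−1 still runs at about 6% to 8% there. The consequence is confined to how far the sensitivity analysis can be trusted as confirmation.

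**What to change.** In the Statistical Analysis section, replace the unqualified robust standard errors with: small-sample bias-corrected robust standard errors (for example Kauermann-Carroll or Mancl-DeRouen), clustered on participant, with a t reference on participants minus 1 degrees of freedom. If an analysis plan already says this, a cross-reference is enough. Since the article reports that analysis is under way, the choice should be recorded before any GEE result is seen.

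Both parts are needed. With divisor n−1 but a normal reference, size is still 6.3% (n=23) to 6.7% (n=18).

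In the balanced layout Kauermann-Carroll reproduces divisor n−1. With the t reference its size is 5.0% under normality, and intervals are 1/0.924 − 1 = 8% (n=23) to 1/0.903 − 1 = 11% (n=18) wider than the uncorrected ones. Mancl-DeRouen multiplies the uncorrected standard error by n/(n−1), a further factor of √(n/(n−1)). Its intervals are about 11% to 14% wider and its size slightly below nominal, 4.5% (n=23) to 4.4% (n=18). In the fitted-GEE simulation it gave 5.3% and 5.4%, within Monte Carlo error.

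The cost is one sentence, a software option and these wider fallback intervals. A participant-level sign-flip permutation test or bootstrap-t interval on each participant's two-eye mean change is an optional extra if the changes prove clearly skewed. It is not needed to correct the wording.
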